The hemodynamic parameters will be collected included the central venous pressure, central venous–arterial blood carbon dioxide partial pressure difference, central venous oxygen saturation, and arterial blood lactate concentration.

All parameters mentioned above will be recorded within 2 h after sepsis diagnosis in the ICU, followed by recording of the ultrasound parameters and hemodynamic parameters once at 24, 72 h, and 7 days.

The prevalence of each phenotype will be described firstly. The primary outcomes are in-hospital and 28-day mortality rates. The secondary outcomes are the degree of echocardiographic improvement on day 7, length of stay in the ICU, and number of days on mechanical ventilation. Severe and irreversible disease will be determined by the supervising physician, and the patient's family chose automatic discharge due to local customary conditions indicating death.

If a respondent is absent at a point in time when access is required, resulting in missing data at that point in time, or if an ending visit is missed, data from other points in time can be included in the analysis for that point in time without affecting the integrity and accuracy of the data at other points in time. We will ensure that the data collection was standardized and controllable, with the advantages of complete information, consistent structure, and no redundant information. In the process of data collection, we use the case report form to extract the clinical information required for the study from the research subjects, convert it into a standardized data form, and construct a reasonable database.

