### Data statistical analysis

SPSS (version 23.0; SPSS Inc., Chicago, IL, USA) will be used for the analysis. Continuous variables will be defined as the mean ± standard deviation, and categorical variables will be presented as percentages. The Kolmogorov–Smirnov test will be used to verify the normality of the distribution of the continuous variables. One-way ANOVA will be used for comparison of means between groups; two independent samples *t*-test will be used for comparison between two groups; χ^2^ test will be used for counting data; and multifactor logistic regression and Cox survival analysis will be used to determine the factors of prognosis. P-values < 0.05 will be considered statistically significant.

The participants will be divided into a modeling cohort and a validation cohort in a 7:3 ratio. In the modeling cohort, variables with *P* < 0.05 in the univariate Cox analysis will be included in the multivariate Cox analysis, and nomogram plots will be constructed. Finally, the validation cohort will be used to evaluate the discrimination ability of the model based on the area under the ROC curve.

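### A family-chosen discharge after a physician's judgement of irreversible disease is taken as death, and nothing limits this to in-hospital mortality, so a patient alive at day 28 could be recorded as dead

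*Protocol article*

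**What the plan says.** All of the relevant text is in the Protocol article, Methods.

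- **Outcomes (Data acquisition):** "The primary outcomes are in-hospital and 28-day mortality rates". One sentence on the secondary outcomes follows.
- **The rule (Data acquisition, next sentence):** "Severe and irreversible disease will be determined by the supervising physician", and the patient's "family chose automatic discharge due to local customary conditions indicating death". Two things are joined here: a clinical judgement by the physician and a decision by the family.
- **Exposure during the stay (Data acquisition):** after the first assessment come further measurements, "followed by recording of the ultrasound parameters and hemodynamic parameters once at 24, 72 h, and 7 days".
- **Missed visits (Data acquisition):** "if an ending visit is missed, data from other points in time can be included in the analysis for that point in time". This concerns reuse of data from other time points. It does not describe a check of vital status after discharge.
- **Use of the outcome (Data statistical analysis):** "multifactor logistic regression and Cox survival analysis will be used to determine the factors of prognosis", with "P-values < 0.05 will be considered statistically significant". A nomogram built from the Cox model and an ROC check in a 30% validation split follow.

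**The concern.** Death by day 28 is a fact that can be established after a patient has left hospital. Under the likely reading of the rule, a judgement plus a family decision takes its place. Every patient who leaves this way and is still alive at day 28 becomes a false death, and 28-day mortality is overstated by that number.

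The comparison between phenotypes could also be affected. The physician who makes the judgement belongs to a team that can see the repeated echocardiograms, and the article expects ultrasound to inform care (Introduction; Discussion). If the appearance of the heart influences the judgement, the exposure helps to create the outcome. The two-reader and expert-panel control under Inclusion criteria covers image interpretation, not outcomes.

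The recorded outcome feeds the logistic model, the Cox model and the nomogram. The validation cohort is a split of the same patients under the same rule, so it shares any misclassification and cannot reveal it.

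In-hospital mortality raises a milder issue: under the rule it becomes a composite of deaths in hospital and departures judged terminal.

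**Working it through.** **No figure to reproduce.** The article gives no rate of automatic discharge and no survival after it. What follows is an illustration under assumptions, not an estimate.

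**Inputs from the article**
- Cohort size 1,152 and 40% prevalence of suppression (Data acquisition): 0.40 × 1,152 ≈ 461 suppressed, leaving 691 others.
- Domestic sepsis mortality 33.5% (Discussion), used as true 28-day mortality in both groups, so that there is no true difference.
- Significance level 0.05, taken as two-sided (sidedness is not stated).

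**Assumed inputs**
- Share leaving under the rule: 15% of suppressed, 5% of others.
- Share of leavers alive at day 28: 20%, range 10% to 40%.

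**Steps for the central case**
1. Leavers: 461 × 0.15 + 691 × 0.05 = 69.2 + 34.6 ≈ 104.
2. False deaths: 104 × 0.20 ≈ 21. These add to the true deaths (0.335 × 1,152 ≈ 386).
3. Recorded mortality: 33.5% + 0.15 × 20% = 36.5% in suppressed, and 33.5% + 0.05 × 20% = 34.5% in others.
4. Spurious difference: (0.15 − 0.05) × 0.20 = 2 percentage points.
5. Standard error: √[0.335 × 0.665 × (1/461 + 1/691)] = 2.84 points.
6. Shift in z: 2 / 2.84 = 0.70. Two-sided rejection probability: P(Z > 1.96 − 0.70) + P(Z < −1.96 − 0.70) ≈ 11%, against 5% with no error.

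**Range**

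| Leaving, suppressed / others | Alive at day 28 | False deaths | Spurious difference | False-positive risk |
|---|---|---|---|---|
| 15% / 5% | 10% | 10 | 1 point | 6% |
| 15% / 5% | 20% | 21 | 2 points | 11% |
| 15% / 5% | 40% | 42 | 4 points | 29% |
| 10% / 10% | 10% to 40% | 12 to 46 | none | 5% |

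If the leaving rates are exchanged (5% of suppressed, 15% of others) with 20% alive, the difference is (0.05 − 0.15) × 0.20 = −2 points: the same size, with the suppressed phenotype looking safer. If nearly every leaver dies before day 28, the 28-day error is close to zero.

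**A second parametrisation** gives a similar answer. Let f be the share of day-28 survivors recorded as dead, so that recorded mortality is m + f(1 − m). With m = 33.5% and f = 5% against 2%, recorded mortality is 36.8% against 34.8%, the odds ratio is 1.09, and the chance of a significant result in that direction is 10% (2.5% without differential error). Misclassification that is equal across phenotypes would dilute a true effect: with f = 10% in both groups, true risks of 40% and 30% (odds ratio 1.56) are recorded as 46% and 37% (odds ratio 1.45).

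**The case against.** The strongest defence is that the rule answers a real problem. Where families customarily take dying patients home, coding them as survivors, or censoring them, would also be wrong and could be worse. That stands. It is why the rule should remain for patients whose status cannot be found, and why a primary analysis counting only confirmed deaths would be a poor replacement: it would miss deaths in families who cannot be reached.

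Several stronger readings are tempting, and the article does not support them.

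- **That the physician alone decides who counts as dead.** The sentence also requires the family's choice to leave, which makes the rule narrower.
- **That the article expressly applies the rule to both primary outcomes.** It names neither, follows the secondary outcomes, and fits in-hospital mortality most naturally. Application to 28-day mortality is inferred from the absence of any limit.
- **That the Cox model will take the discharge date as the death date.** Nothing is said about event dates, time origin or censoring, and such detail may be in the full protocol or analysis plan.
- **That the lack of stated masking or sensitivity analyses is itself an error.** A condensed article commonly leaves these to the full document. The finding rests on the stated equation of discharge with death.
- **That suppressed phenotypes will look deadlier.** The Introduction and Discussion link ultrasound to resuscitation and organ support, not to a judgement of irreversibility. The Discussion presents reversibility as a main feature of septic suppression, so a physician of that view need not regard a suppressed heart as hopeless.

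**Conclusion.** The point holds in a limited form. The article states a rule under which a patient judged irreversible and then taken home by the family is treated as dead. It does not confine that rule to in-hospital mortality, so under the likely reading a patient alive at day 28 can be recorded as a 28-day death. This is a stated definition of a primary outcome, not an omission.

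Dependence on phenotype is possible because the treating team can see the echocardiograms, but it is not shown. The central illustration (2 points, about 11% false-positive risk) rests on assumed leaving rates of 15% and 5% and an assumed 20% alive at day 28. Other assumptions give no difference or one of opposite sign. The figures show that the issue can matter in a cohort of 1,152; they do not estimate the bias in this study.

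**What to change.** 1. State whether the rule applies to in-hospital mortality, 28-day mortality or both, and reword the sentence so that both conditions are clear.
2. Record automatic discharge as its own category, with its date.
3. For 28-day mortality, ascertain vital status at day 28, and date of death where applicable, for each patient who leaves this way, and use it where known.
4. Where day-28 status remains unknown, keep the sponsor's rule (count as dead) and add a bounding analysis that counts these patients as alive.
5. For in-hospital mortality, keep the composite but report death and automatic discharge separately by phenotype.

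The cost is one extra outcome category, a follow-up contact for these patients, and a little more analysis. Some families will not be reached; the bound in step 4 shows how much that matters. Patient care is unchanged.

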### Data statistical analysis

SPSS (version 23.0; SPSS Inc., Chicago, IL, USA) will be used for the analysis. Continuous variables will be defined as the mean ± standard deviation, and categorical variables will be presented as percentages. The Kolmogorov–Smirnov test will be used to verify the normality of the distribution of the continuous variables. One-way ANOVA will be used for comparison of means between groups; two independent samples *t*-test will be used for comparison between two groups; χ^2^ test will be used for counting data; and multifactor logistic regression and Cox survival analysis will be used to determine the factors of prognosis. P-values < 0.05 will be considered statistically significant.

The participants will be divided into a modeling cohort and a validation cohort in a 7:3 ratio. In the modeling cohort, variables with *P* < 0.05 in the univariate Cox analysis will be included in the multivariate Cox analysis, and nomogram plots will be constructed. Finally, the validation cohort will be used to evaluate the discrimination ability of the model based on the area under the ROC curve.

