**Methods:**

This was a multicenter, prospective cohort study. The study population will consist of all eligible consecutive patients with sepsis or septic shock who meet the Sepsis 3.0 diagnostic criteria and were aged ≥18 years. Clinical data and echocardiographic measurements will be recorded within 2 h, at the 24th hour, at the 72nd hour, and on the 7th day after admission. The prevalence of each phenotype will be described as well, and their association with prognosis will be analyzed statistically.

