### Data acquisition

This study has been approved by the local ethics committee of every participated center. The continuous inpatient electronic medical records will be reviewed for sepsis between April 2022 to April 2025. The prevalence of septic myocardial suppression has been reported in previous literature as 10–70% (4), taking the middle value of 40%. With a 95% confidence level, the results were required to fall within 10% of the overall truth rate, and the required sample size was estimated to be at least 1,152 cases. Detailed demographic and clinical characteristics will be collected and recorded, including age, sex, height, weight, primary diagnosis, site of infection, etiology (if known), underlying disease (hypertension, diabetes, coronary artery disease, chronic kidney disease, chronic obstructive pulmonary disease, oncologic disease, autoimmune disease, etc.), and medication history (beta-blockers, digitalis analogs, hormones, immunosuppressive agents, antineoplastic drugs, etc.).

Clinical and laboratory data will be collected included temperature, heart rate, respiratory rate, peripheral oxygen saturation, blood pressure (systolic/diastolic), pH, partial pressure of oxygen, inspired oxygen concentration, Glasgow Coma Scale score, white blood cell count, neutrophil count, lymphocyte count, hematocrit level, platelet count, calcitonin level, G-test scores, serum albumin level, total bilirubin level, serum creatinine level, troponin I level, NT-proBNP level, maximum dose of vasoactive drugs (norepinephrine, dopamine, vasopressin) or cardiac drugs (dobutamine, levosimendan, desacetyl trichothecene), SOFA score, and APACHE II score.

The ultrasound parameters are as follows:

Indicators of left ventricular systolic function: mitral annular plane systolic excursion (MAPSE), LVEF, and left ventricular outflow tract flow velocity time integralIndicators of left ventricular diastolic function: E, A, and *e*'Right ventricular function indicators: tricuspid annular plane systolic excursion (TAPSE), inferior vena cava end-expiratory and end-inspiratory internal diameters, and right/left heart diastolic basal segment transverse diameter ratio (apical four-chamber heart view)Basal status indicators: right ventricular free wall thickness (subxiphoid four-chamber cardiac section) and septal thickness (apical four-chamber cardiac section).

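### The only methods named for comparing means are unadjusted, so phenotype differences in the continuous secondary outcomes may be confounded by baseline differences

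*Protocol article*

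**What the plan says.** The abstract (Methods) gives the design: "This was a multicenter, prospective cohort study". Phenotype is observed, not assigned.

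The section Data acquisition separates two kinds of outcome. On mortality: "The primary outcomes are in-hospital and 28-day mortality rates". On the rest: "The secondary outcomes are the degree of echocardiographic improvement on day 7, length of stay in the ICU, and number of days on mechanical ventilation".

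The section Data statistical analysis then lists methods by type of variable. For means: "One-way ANOVA will be used for comparison of means between groups". For two groups it gives the independent-samples t-test ("test will be used for comparison between two groups"). Counts get a chi-squared test. The multivariable methods are stated in one clause: "multifactor logistic regression and Cox survival analysis will be used to determine the factors of prognosis". A Cox-based nomogram follows. No linear, covariance, count or mixed model is named.

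Data acquisition also lists baseline variables that could serve for adjustment: age, sex, infection site, underlying diseases, and "SOFA score, and APACHE II score". They are to be recorded within 2 h of the sepsis diagnosis in the ICU.

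**The concern.** ANOVA and the t-test take no covariates. In a cohort, patients with different phenotypes may also differ in age, comorbidity, source of infection and severity, and each of these may affect time in the ICU, ventilation and cardiac recovery.

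The protocol's own Discussion makes this concrete for one outcome. It says that respiratory distress syndrome and mechanical ventilation affect right ventricular function by raising afterload. Respiratory failure can therefore help produce the right ventricular phenotype and also lengthen ventilation. A crude comparison of ventilator days between patients with and without that phenotype would mix the two. The Introduction likewise suggests that a hyperdynamic left ventricle may reflect unresolved vascular paralysis, which is a feature of the sepsis itself.

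At stake is the interpretation of the secondary results. A crude difference could be reported as a consequence of the phenotype, and it could disagree with the adjusted mortality results only because one analysis was adjusted and the other was not.

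**Working it through.** The plan gives no figure on this point, so there is none to reproduce. The check has two parts.

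**1. Outcomes against named methods**

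| Outcome | Named adjusted model that fits | Named method for a mean |
|---|---|---|
| In-hospital and 28-day mortality | Logistic, Cox | Not needed |
| ICU stay | Cox is possible, but the text does not say so | ANOVA, t-test |
| Ventilator days | None fits naturally | ANOVA, t-test |
| Degree of improvement on day 7 | None, unless dichotomised by a rule not described | ANOVA, t-test |

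**2. How far an unadjusted test can mislead**

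Inputs from Data acquisition: N = 1,152 and a suppression prevalence of 40%, so 0.40 × 1,152 ≈ 461 against 691. The significance level of 0.05 is from Data statistical analysis; I take it as two-sided, which is not stated.

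Inputs assumed, because the documents give none: a baseline gap of 1.5 SOFA points, 0.4 day of outcome per point, an outcome SD of 6 days, and no true phenotype effect.

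- Bias in the crude difference = 1.5 × 0.4 = 0.6 day, which is 0.1 SD.
- SE = 6 × √(1/461 + 1/691) = 0.36 day.
- Shift = 0.6 / 0.36 ≈ 1.66 standard errors.
- Chance of a significant result = P(Z > 1.96 − 1.66), with a negligible lower tail, ≈ 38% instead of 5%.
- Low end, 1 point × 0.3 day = 0.3 day: about 13%. High end, 2 points × 0.5 day = 1.0 day: about 79%.

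The same check in SD units lets *g* be the severity gap between groups and *r* the severity–outcome correlation, so that bias = *g* × *r*. Group sizes are as above, with no true effect:

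| *g* | *r* | Bias (SD) | Crude test significant |
|---|---|---|---|
| 0 | any | 0 | 5% |
| 0.2 | 0.1 | 0.02 | 6% |
| 0.2 | 0.3 | 0.06 | 17% |
| 0.5 | 0.3 | 0.15 | 70% |
| 0.5 | 0.5 | 0.25 | 99% |

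A simulation of 1,000 repeats per setting gave similar rates for the t-test (15%, 74% and 99% in the last three rows). A linear model adjusted for the simulated severity variable stayed at about 4% to 6%.

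With an assumed true effect of 0.30 SD, the crude difference averaged 0.34 SD (*g* = 0.2, *r* = 0.2) or 0.45 SD (*g* = 0.5, *r* = 0.3). Confounding is then 0.04/0.34 ≈ 12% or 0.15/0.45 ≈ 33% of what would be reported.

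Two limits apply. The simulated adjustment uses the true confounder measured without error, so real adjustment will remove less. If severity shortens rather than lengthens the outcome, the bias changes sign, while the two-sided rejection rate is the same by symmetry.

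**The case against.** The strongest reply is that the methods section is a generic list. It does not assign ANOVA or t-tests to ICU stay, ventilator days or day-7 improvement by name, and the same tests could be meant for describing baseline characteristics. Prognosis need not mean mortality alone. A journal article is condensed, and a fuller protocol or analysis plan may hold the adjusted secondary models. This stands in part: the link is an inference. But the article does not leave the matter open. It states methods for means, all of them unadjusted, and the adjusted models it states do not suit at least two of the three secondary outcomes. The point concerns what is written, not a missing detail.

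A reader might also infer that the phenotype differences would mainly reflect baseline severity, or that they are confounded by design. The documents do not support that. They give no severity gap between phenotypes and no severity–outcome relation, and the working above runs from no bias to a dominant one. In the central illustration the bias is only 0.1 SD, and the test is non-significant in 62% of repeats.

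The direction is also open. The Discussion cites sepsis mortality of 33.5% and of 34 to 56%, and early death shortens both ICU stay and ventilation. It also cites a study in which patients with a reversible fall in ejection fraction did better than those without one.

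Finally, adjusting for SOFA or shock can be disputed. Both partly measure circulatory failure, which the cardiac phenotype may itself cause, and they are recorded alongside the first echocardiogram. That objection stands and shapes the fix.

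**Conclusion.** The point holds in limited form. In this non-randomised cohort the only methods named for comparing means are unadjusted, and the named adjusted models do not naturally cover day-7 improvement or ventilator days. Read as written, phenotype differences in the continuous secondary outcomes may be confounded by baseline differences. The documents fix neither the amount nor the direction.

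The 38% figure and its 13% to 79% range show that, at this sample size, moderate imbalance would be enough to mislead. They are not estimates for this study, because the SOFA gap, the slope and the SD are all assumed. The conclusion also rests on reading the tests for means as applying to the continuous secondary outcomes, which is the natural reading but not an explicit statement. The mortality analyses, for which adjusted models are named, are not affected.

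**What to change.** State, for each secondary outcome, a regression on baseline phenotype of a type suited to that outcome, adjusted for a covariate set fixed before analysis from variables already collected:

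- **Main model:** age, sex, infection site and main comorbidities. For day-7 improvement, add the baseline value of the echocardiographic measure, because groups defined by an abnormal value will tend to move back toward the mean.
- **Sensitivity model:** add SOFA or APACHE II and septic shock. Keep these out of the main model because they may partly reflect the cardiac phenotype. Shock is not listed as a recorded item; it would be derived from vasoactive drug use and lactate under the definition in Inclusion criteria. Comparing the two models shows how far the result depends on severity.
- **Descriptive use:** keep ANOVA and t-tests for descriptive comparisons, and label any crude outcome contrast as unadjusted.

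This needs a change of wording and no new data. The cost is slightly more analysis work and the need to choose the covariates in advance.

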
## Methods

### Inclusion criteria

The present study will be conducted in several medical centers in China, including Fujian Provincial Hospital, West China Hospital of Sichuan University, Peking Union Medical College Hospital, Fourth Hospital of Hebei Medical University, Chinese PLA General Hospital, First Peopl*e*'s Hospital of Hangzhou City Affiliated to Zhejiang University, First Affiliated Hospital of Xiamen University, Shandong Provincial Hospital Affiliated to Shandong First Medical University, the Affiliated Hospital of Qingdao University, Quanzhou First Hospital affiliated to Fujian Medical University, the First Affiliated Hospital of Anhui Medical University, between April 2022 to April 2025. Informed consent will be obtained from all patients or their legal guardians. All patients with sepsis or septic shock who diagnosed using the Sepsis 3.0 diagnostic criteria (1) and were ≥18 years of age who admitted or hospitalized to each center will be included. Sepsis is defined as an increasing of ≥2 points from baseline in the Sequential Organ Failure Assessment (SOFA) score due to infection, and septic shock is defined as persistent hypotension on top of sepsis, requiring vasoactive drugs to maintain a mean arterial pressure ≥65 mmHg and a blood lactate level >2 mmol/L despite adequate fluid resuscitation. Patients will be admitted to the ICU, and transthoracic echocardiograms will be performed by relevant qualified personnel and interpreted by two qualified personnel. Two senior sonographers (A and B) will independently examine the patients and compare them to identify the true positives as accurately as possible. The agreement rate between the two specialists is as high as 100%, and the reconfirmation of the individual set with doubts reach a unified conclusion. In case of diagnostic disagreement, we will ask an expert panel for a resolution, and as a quality control, all ultrasound images and measurements of each enrolled patient will be recorded. In addition, the results will be compared with the latest guidelines before building the dataset. Patients eligible for inclusion will have their first echocardiogram examination completed within 2 h of admission. If eligible, informed consent will be required prior to formal study entry.

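### The stated tests and models do not account for centre, so the crude phenotype–mortality comparisons can be confounded by hospital

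*Protocol article*

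**What the plan says.** The Methods part of the Abstract gives the design: "This was a multicenter, prospective cohort study". Under Inclusion criteria, the article says "The present study will be conducted in several medical centers in China" and then names 11 hospitals.

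Under Data acquisition, "The primary outcomes are in-hospital and 28-day mortality rates". The same section appears to count as a death a discharge chosen by the family of a patient whom the supervising physician judges to have severe, irreversible disease, and it refers to local custom in doing so. Phenotype prevalence is to be described; no interval is specified. The list of recorded variables does not include centre.

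The sample size, also under Data acquisition, takes a prevalence of 40%. It continues: "With a 95% confidence level, the results were required to fall within 10% of the overall truth rate". From these inputs the article reports its result as follows: "the required sample size was estimated to be at least 1,152 cases". It mentions neither an intracluster correlation nor a design effect.

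Under Data statistical analysis, group comparisons use one-way ANOVA, the two-sample t-test and chi-square. For prognosis, "multifactor logistic regression and Cox survival analysis will be used to determine the factors of prognosis". In the modelling cohort, variables with univariate P<0.05 go into the multivariable Cox model. Centre is not mentioned.

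**The concern.** The central question is whether the ultrasound phenotype is associated with death. The tests named treat all patients as independent draws from one population. Patients in the same hospital share case mix, care, imaging conditions and conventions for classifying outcomes.

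The article itself gives a reason to expect the outcome to differ by site, because the classification of some deaths depends on a local physician's judgement and on custom. It also says, in its statement of limitations, that transesophageal imaging was not used where transthoracic data were unavailable because of constraints at each centre, so the selection of patients may differ too.

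If hospitals with more of a given phenotype also happen to record more deaths, a pooled test will report an association that exists in no single hospital. The univariate P<0.05 rule does not guarantee centre a place in the Cox model, and centre is not on the list of variables from which the rule would choose.

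**Working it through.** **Inputs from the article.** N = 1,152; 11 hospitals; prevalence p = 0.40; 95% confidence; mortality 33.5% (the domestic figure in the Discussion). Equal centre sizes are assumed, so m = 1,152/11 = 104.7. The article gives no ICC or between-centre SD, so every value below is an assumption shown over a range.

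**The plan's own figure.** With n = 1.96² × p(1−p)/d²:
- d = 0.10 (10 points, absolute): 3.8416 × 0.24/0.01 = 92.2, so 93.
- d = 0.04 (10% of 40%, relative): 3.8416 × 0.24/0.0016 = 576.2, so 577.

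Neither gives 1,152. Twice 576.2 is 1,152.4, so the figure matches an unexplained doubling of the relative version. A doubling would fit a design effect of 2, that is, an ICC of 1/(104.7−1) = 0.0096, but the article does not say so.

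**Phenotype against mortality.** Trials were simulated with 11 equal centres, 40% phenotype prevalence, 33.5% mortality and no phenotype effect within any centre. The log-odds of phenotype and of death each varied between centres with the same SD. There were 20,000 trials per scenario with 105 patients per centre, at a nominal 5% level.

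| Logit SD | ICC at p = 0.40 | Crude chi-square, independent centre effects | Crude chi-square, correlation 0.5 | Mantel-Haenszel by centre |
|---|---|---|---|---|
| 0.2 | 0.009 | 5.1% | 5.2% | 4.8% |
| 0.3 | 0.02 | 5.4% | 6.5% | 4.9–5.0% |
| 0.5 | 0.05 | 8.2% | 16.4% | 4.8% |
| 0.7 | 0.10 | 15.3% | 36.5% | 5.0% |

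For scale, an SD of 0.3 puts 95% of hospitals at a prevalence of about 27% to 55%; an SD of 0.7 puts them at about 15% to 73%.

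**Prevalence interval, if one is reported.** Design effect DE = 1 + (104.7−1) × ICC. Half-width = 1.96 × √(0.24 × DE/1,152). Coverage of an interval that ignores clustering = 2Φ(1.96/√DE) − 1.

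| Assumed ICC | DE | Half-width (points) | Coverage of unclustered 95% interval |
|---|---|---|---|
| 0 | 1.00 | 2.8 | 95% |
| 0.01 | 2.04 | 4.0 | 83% |
| 0.02 | 3.07 | 5.0 | 74% |
| 0.05 | 6.19 | 7.0 | 57% |
| 0.10 | 11.37 | 9.5 | 44% |

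If the 10% target is relative (±4 points), 1,152 patients meet it only up to an ICC of about 0.01. If it is absolute (±10 points), it is met throughout this table.

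**The case against.** The strongest objection is that this is a condensed article and the analysis plan is not shown. Logistic and Cox models both admit a centre term or stratum, and the article does not say that centre is left out. That stands as a limit on severity: centre may be handled in a document not seen here. It does not remove the point. The article names tests that assume independence and a covariate rule that gives centre no assured place, and following them as written leaves centre out.

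Second, the simulation concerns the crude chi-square, not the multivariable models. Severity scores, infection site and comorbidities are collected and could absorb part of the case-mix difference. This also stands: the figures show no bias in the adjusted models. Those covariates would not, however, capture differences in how death is classified.

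Third, reading differences between sites are limited by two independent senior sonographers and an expert panel. That is fair for measurement, but it does not address case mix, care or outcome classification.

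Fourth, the size depends on heterogeneity that the documents do not quantify. At a logit SD of 0.3 or less the inflation is small, and with independent centre effects 15% needs an ICC near 0.10.

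Two stronger readings are tempting and not supported. A reader might infer that the plan's prevalence intervals are too narrow, but it specifies none. A reader might also infer that 1,152 ignores clustering as a simple-random-sample figure. Simple random sampling gives 93 or 577, and the unexplained factor of 2 is compatible with an unstated design effect.

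**Conclusion.** The point holds in this form: the stated methods do not account for centre, and the crude phenotype–mortality tests can therefore be confounded by hospital. This is a conditional risk and not a demonstrated error. It needs both phenotype frequency and recorded mortality to vary between hospitals.

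With independent centre effects the inflation runs from negligible (logit SD 0.2–0.3) to about three times the nominal level (SD 0.7), and further if the effects are correlated. For prevalence, the consequence attaches to any interval that is later calculated without clustering. These sizes rest on assumed ICCs and SDs, equal centre sizes and 11 centres. The matter is worth correcting because the remedy is cheap, but the possibility that an unseen plan already covers it keeps the severity moderate.

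**What to change.** 1. Add centre to the recorded variables.
2. Stratify the prognostic Cox models by centre, or use a shared frailty, regardless of the univariate P<0.05 rule.
3. Include a centre effect, fixed or random, in the logistic models.
4. Use a centre-stratified Mantel-Haenszel test in place of the crude chi-square for phenotype against mortality.
5. If a prevalence interval is reported, adjust it for clustering with a method suited to about 11 centres. Report the ICC and show prevalence by centre.
6. State where the factor of 2 in 1,152 comes from and whether the 10% is absolute or relative.

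The cost is wording in the analysis section, one recorded variable and a little more analysis work. Intervals will be slightly wider where centres differ little, and wider in step with the ICC where they differ more. No extra patients or procedures are needed.
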